#### Withdrawal and termination criteria

2.3.3

Withdrawal criteria: (1) Individuals unable to complete the entire treatment and observation process; (2) Individuals who cannot fully understand the various forms and questionnaires provided during the study and require assistance; (3) Individuals concurrently receiving other treatments; (4) Individuals with poor compliance; (5) Individuals with incomplete data affecting efficacy and safety evaluation; (6) Individuals experiencing severe adverse reactions or complications who are unsuitable for continued treatment and are therefore withdrawn from the trial; and (7) Individuals who have not completed more than 2/3 of the treatment course (including those withdrawn from the trial and lost to follow-up).

Termination criteria: Participants experiencing severe adverse events or reactions making it inappropriate to continue in the study; major errors found in the study design or significant deviations from the facts; participants who develop serious complications or deteriorate in a condition requiring emergency measures; participants withdrawing from the clinical study; patients who are uncooperative or noncompliant with treatment, despite repeated explanations from clinicians; during the trial, researchers should retain all original trial records and document in detail the reasons and timing for withdrawal. Those who have completed more than half of the treatment regimen should be included in the efficacy statistics.

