### Randomization, allocation concealment, and blinding

2.4

Eligible patients will be randomly assigned to two groups: the treatment group (receiving warm needle acupuncture combined with Western medicine) and the control group (receiving electro-acupuncture). The randomization will be performed using the CHISS software for block randomization. The size of each block is n. Once the randomization scheme is generated, it will be kept by a third party independent of this study. To ensure allocation concealment, we use sealed opaque envelopes. These envelopes are prepared by an independent member of the research team, and participants draw an envelope randomly upon enrollment in the study to determine their treatment group. Clinical researchers will obtain the specific treatment plan for each patient through designated channels (such as by phone). Assessors will not be informed of the participants’ specific group assignments throughout the follow-up period. All assessment work will be carried out by assessors independent of the treatment process. These assessors will receive rigorous training before the study begins to ensure their standardized understanding and application of the VAS score, thereby ensuring the consistency and accuracy of the assessments. Assessors will be strictly restricted from accessing participants’ treatment group information throughout the follow-up period to maintain assessor blinding. Blind statistical analysis will also be implemented during the data aggregation and analysis phase, with statisticians remaining unaware of the participants’ treatment allocations to ensure the objectivity of the statistical analysis results. In the event of serious adverse events, emergency medical situations, or requests from participants, the sealed envelope containing the blinding information will be opened by an independent third party, and the reasons, time, and personnel involved in the unblinding will be recorded in detail and reported to the relevant committee promptly. Medical decisions will be made based on the unblinding results, and participants will be allowed to withdraw from the trial if necessary.

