### Safety assessment

2.9

During the study, observations and records will be made of any potential adverse reactions, such as bleeding caused by acupuncture, hematoma, needle sickness, pain at the acupuncture site, infection, as well as skin rupture and infection after moxibustion. The primary records will include the incidence rate of adverse events and the grading of safety evaluations. Adverse events will be graded according to the Common Terminology Criteria for Adverse Events (CTCAE) Version 5.0. Mild (Grade 1): asymptomatic or mild symptoms, requiring no intervention; Moderate (Grade 2): symptoms are evident and require non-invasive treatment (such as local hemostasis, disinfection, etc.); Severe (Grade 3 and above): symptoms are severe, requiring hospitalization or leading to discontinuation of treatment. The evaluation time points are detailed in Table 1.

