The success of assessor blinding will be evaluated using James’ blinding index. A value close to 0.5 indicates effective blinding (0 = completely unblinded; 1 = completely blinded). If there are baseline differences (e.g., age, baseline VAS score), adjustments will be made using analysis of covariance (ANCOVA). Pre-specified subgroups (e.g., age < 50 vs. ≥ 50 years, baseline VAS score severity) will be explored using interaction terms in regression models. *p*-values will be adjusted using the false discovery rate (FDR) correction for multiple comparisons for the primary outcome.

Adverse events (AE) will be graded according to CTCAE v5.0. The incidence rates between groups will be compared using the chi-square test (or Fisher’s exact test for rare events). Descriptive analysis will be conducted for serious adverse events (≥ grade 3). Analyses will be performed using SAS 9.4 (SAS Institute) and SPSS 26.0 (IBM Corp). Continuous outcomes will be reported as mean differences (MD) with 95% CI and effect sizes (Cohen’s d). Categorical outcomes will be reported as risk ratios (RR) with 95% CI. Exact *p*-values will be provided for all tests, with a significance level set at *p* < 0.05 for the primary outcome.

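### Section 2.12 defines serious adverse events by severity grade (CTCAE grade 3 or above), so the serious-event summary can misclassify events

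*Protocol article*

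**What the plan says.** Four places in the protocol article bear on this.

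- Section 2.12 (Statistical analysis) names the scale: "Adverse events (AE) will be graded according to CTCAE v5.0". It then fixes what counts as serious: "Descriptive analysis will be conducted for serious adverse events (≥ grade 3").
- Section 2.9 (Safety assessment) sets out three classes on that scale. The middle one is "Moderate (Grade 2): symptoms are evident and require non-invasive treatment (such as local hemostasis, disinfection, etc".) and the top one is "Severe (Grade 3 and above): symptoms are severe, requiring hospitalization or leading to discontinuation of treatment".
- Section 2.4 (Randomization, allocation concealment, and blinding) uses the word *serious* as one of the triggers for breaking the blind: "In the event of serious adverse events, emergency medical situations, or requests from participants, the sealed envelope containing the blinding information will be opened".
- Section 2.3.3 (Withdrawal and termination criteria) uses the word *severe* as a ground for termination: "Participants experiencing severe adverse events or reactions making it inappropriate to continue in the study".

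No section of the article defines seriousness by what happened to the participant.

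**The concern.** Severity and seriousness are different attributes of an adverse event. Severity is its intensity, which is what the mild, moderate and severe classes of section 2.9 express. Seriousness depends on the event's outcome, such as death, threat to life, new or prolonged hospitalisation, or lasting disability. Section 2.12 makes the first stand for the second. Section 2.9 also writes a third attribute, stopping treatment, into the description of the top severity class.

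This is a definition that the article states, so it cannot be set aside as detail left to a fuller document. Evaluating safety is a stated objective. The two arms also carry different local risks: moxibustion heat in one and electrical current in the other. A table headed serious adverse events should show serious outcomes by arm, and it should not absorb differences in tolerability.

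**Working it through.** The point concerns definitions, and the plan has no figure to reproduce. The check sets the passages side by side and asks how each kind of event would be classed.

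**Step 1: one cut-off, several roles.** Section 2.9 calls grade 3 and above *severe*; section 2.12 calls the same set *serious*. The section 2.9 description of that set also names hospitalisation (an outcome) and discontinuation of treatment (an action taken). A single threshold therefore carries severity, seriousness and discontinuation.

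**Step 2: a severe event that only stops acupuncture.** It meets the section 2.9 description through its second alternative, without hospitalisation. Section 2.12 then counts it as serious although no serious outcome has occurred. This is over-counting, and it follows directly from the text.

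**Step 3: a moderate event that stops treatment.** By intensity it fits grade 2, whose description does not mention discontinuation. By consequence it may fit grade 3 or above. Whether discontinuation is sufficient depends on how the section 2.9 sentence is read, since that sentence opens by requiring severe symptoms. Two assessors could class the same event differently, and with the section 2.12 rule they would then differ on whether it is serious.

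**Step 4: an event serious by outcome but graded below 3.** Section 2.9 already places events that require hospitalisation in grade 3 or above, so most such events are captured. The gap is a prolonged existing stay. Section 2.2 recruits inpatients, and section 2.6 starts treatment on the second day after surgery. A moderate event that lengthens the stay of someone already in hospital is not clearly covered and could be left out. This is under-counting, and it is narrower than the over-counting in step 2.

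**Step 5: the same words elsewhere.** Section 2.3.3 makes a severe event a ground for ending participation, while section 2.9 makes discontinuation part of the description of a severe event. Each refers to the other. Section 2.4 uses *serious* without saying whether the section 2.12 meaning applies.

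**Step 6: size.** The documents give no adverse-event rates, so the number of misclassified events cannot be computed. The only available figure is the weight of one participant. Section 2.5 gives 48 per arm, so one reclassified participant moves that arm's rate by 1/48 = 0.0208, or 2.1 percentage points.

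**The case against.** The strongest reply is that this is a slip in one parenthesis. Section 2.9 uses *severe* for the class, section 2.3.3 speaks of severe events, and *serious* in section 2.12 may simply be loose usage. The affected output is descriptive. Section 2.3.3 requires the reasons and timing of withdrawal to be documented and section 2.9 grades each event, so grade 3 or above counts and withdrawals could be tabulated separately from data already planned. Full outcome criteria and form fields usually sit in the full protocol.

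Much of this stands. It limits the consequence and makes the correction cheap. It does not remove the defect, because the article states a rule, and following that rule gives a wrong serious-event summary. Whether loose usage was meant cannot be confirmed from the text.

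A reader might also infer more than the documents support:

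- **That mild events which stop treatment become serious.** Section 2.9 opens its top class by requiring severe symptoms and gives mild events a class of their own. A mild event that stops treatment is not plainly grade 3.
- **That tolerability dropouts would dominate the table.** The 15% allowance in section 2.5 (0.15 × 48 = 7.2 per arm) is for dropout from any cause. Section 2.3.3 lists many causes unrelated to adverse events, so the allowance says nothing about adverse-event rates.
- **That the grade 3 cut-off drives unblinding.** Section 2.4 does not cite it, and it lists emergencies and participant requests as further triggers. The report it requires concerns the unblinding itself.
- **That the less tolerable arm would appear to cause more serious harm.** This is possible in principle, but without event rates by arm it cannot be asserted.

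**Conclusion.** The point holds at moderate weight. Section 2.12 uses a severity grade as the definition of serious adverse events, and section 2.9 ties that grade to discontinuation. The clearest consequence is that severe events which only stop acupuncture are counted as serious. Moderate events that stop treatment have no clear class. Leaving out an event that is serious by outcome is possible but narrow, since hospitalisation already falls in grade 3 or above.

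The extent is unknown; the only supportable figure is 2.1 percentage points of an arm's rate for each reclassified participant, assuming all 48 per arm form the denominator. The primary outcome, alpha and power are untouched, and the affected summary is descriptive. The conclusion assumes that the section 2.12 definition would be applied as written and that no outcome-based definition in a fuller document overrides it.

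**What to change.** - In section 2.12, drop the grade 3 parenthesis as the definition of serious. Define seriousness by outcome criteria (death, life-threatening event, new or prolonged hospitalisation, lasting disability, other medically important event), separately from CTCAE grade.
- In section 2.9, take discontinuation of treatment out of the grade description. Record discontinuation due to an adverse event as its own variable.
- Report three summaries by arm: serious events, grade 3 or above events, and events leading to discontinuation.
- Reconcile the use of *severe* and *serious* in sections 2.3.3, 2.4, 2.9 and 2.12, so that each passage states which attribute it means. The clinical rules for stopping and unblinding remain for the investigators to settle.

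The cost is a wording amendment, minor changes to the adverse-event form and slightly longer safety tables. Section 2.14 says that enrolment has begun, so an early change limits the re-coding of events already recorded.

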### Dissemination

2.13

The results of the study will be presented at scientific conferences and in peer-reviewed publications. Participants included in the study will also have the opportunity to obtain the study results by telephone or e-mail.

### Trial status

2.14

Currently, the protocol is version 1.0, registered on 31 August 2024. At the time of protocol submission, potential participants of the study have been actively enrolled.

## Discussion

3

This experiment is a single-center, prospective, randomized, patient-assessor-blinded, controlled trial that aims to evaluate the effectiveness and safety of UA combined with WA in treating residual numbness after LDH surgery. From a modern medical perspective, it falls under the category of peripheral nerve disorders.

Drawing from the perspective of traditional Chinese medicine (TCM) pathogenesis and building on our prior clinical practice, we have, for the first time, applied UA combined with WA to treat postoperative numbness. UA is an emerging therapy established by [name]. Its theoretical basis is completely rooted in traditional Chinese culture. UA is different from traditional acupuncture, which is a therapeutic method to treat diseases by acupuncture at the umbilical point in a certain way based on the theory of bioholography (33). Compared with other acupuncture methods, umbilical acupuncture (UA) regulates the body’s qi and blood through the holographic reflex zones of the umbilicus, characterized by fewer acupoints and milder stimulation. Electro-acupuncture primarily exerts its effects through local nerve regulation, with relatively weak overall regulatory effects on systemic functions. Warm needle acupuncture that combines moxibustion and acupuncture has become increasingly popular due to its significant clinical efficacy and safety (34). This approach treats both the symptoms and the root causes, with a particular emphasis on addressing the underlying causes. Some studies have shown that WNA has better effects in relieving pain and promoting blood circulation compared with simple acupuncture or moxibustion (35). The therapeutic mechanism of WA is similar to the process of thermotherapy, in which a high-temperature area is formed locally in a tissue to promote metabolism, enlarge blood vessels, and reduce the excitability of peripheral nerves (34). The stimulus from needles in acupuncture involves a change of temperature and heat transfer through tissue. Both ambient and body temperatures influence the effect of acupuncture, this stimulus may result in the regulation of homeostasis (36). Comparing the physical efficiency of acupuncture needles regarding heat transfer with the daily energy consumption of a human body reveals an interesting and new aspect: Applying the normal energy consumption rate of a human body to CO3 domain volume results in 0.00003262 W, showing that the amount of energy conveyed by acupuncture needles is much higher than the body’s energy consumption and suggesting a strong stimulating effect in the regulation of homeostasis (36). UA and WA are widely used in clinical practice and have been proven safe (33).

According to domestic literature reports, electroacupuncture has a definite therapeutic effect in treating residual pain and numbness after percutaneous transforaminal endoscopic discectomy (PTED) for LDH. The overall effective rates for pain and numbness relief are 95.45 and 92.86%. The overall efficacy of combined electroacupuncture treatment is superior to that of Western medicine treatment alone (37). Some other articles have reported that low-frequency EA was applied directly to the spinal nerve root at right L4, L5, and, S1, immediately after treatment, right or left back and lower extremity pain and numbness were markedly reduced. The walking distance of patients was also greatly extended. The mechanisms underlying this effect may be attributed to inhibitory control at the spinal level, inhibition of potential activity by hyperpolarization of nerve endings, or changes in nerve blood flow (38, 39).

Therefore, we have established an electroacupuncture control group. We will compare this treatment with electroacupuncture therapy to explore a potentially more effective acupuncture treatment regimen that promotes early rehabilitation for patients with numbness after LDH surgery. We hope to find a better acupuncture treatment method to guide clinical practice and improve treatment outcomes. In addition, this study may provide more scientific evidence for non-pharmacological treatments and facilitate future related research.

This study has certain limitations. Its single-center design may not fully represent the clinical practice situation across multiple centers. The VAS (Visual Analog Scale) score is a subjective outcome measure that is susceptible to individual differences and psychological factors among patients. The follow-up period of this study is 6 months, which may not be sufficient to fully assess the long-term effects of the treatment. Insufficient sample size may affect the statistical power of the results, and there may be issues with poor patient compliance and high dropout rates in the study.
